### Intervention

Curricula for both interventions, IMPower and SOS, were developed specifically by NMNW to target younger adolescents in Nairobi [32, 33]. Both girls’ and boys’ interventions were taught in six two-hour sessions held weekly on school property. Sessions in the intervention included role-plays, facilitated discussions, and verbal and physical skills practice.

The girls’ intervention focused on empowerment, avoiding risky situations, verbal skills, and physical self-defense. Specific session topics included: (1) building rapport and self-esteem and providing definitions and objectives; (2) personal awareness, self-efficacy, boundaries, and assertive communication skills; (3) verbal and physical defense skills; (4) review of verbal and physical skills and skills practice using bags and mitts; (5) de-escalation and negotiation, and more advanced defense techniques for use in instances such as multiple or armed attackers; (6) review of all previous sessions and a discussion of sexual assault and harassment experiences.

The boys’ training focused on promoting gender equality, developing positive masculinity, and teaching safe and effective bystander intervention techniques [29]. This intervention was different from a previously-studied version of the intervention in order to incorporate learnings from implementing the previous intervention. Specific session topics included: (1) building rapport and develop awareness about gender interactions; (2) personal awareness, learning assertive body language and verbal response; (3) intervention, verbal and physical defense skills; (4) defining and understanding sexual consent, valid consent, causes and myths about rape, de-escalation and negotiation techniques; (5) responsibility for one’s actions and behaviors, practice using intervention skills; (6) reviewing key concepts; reinforcing skills through role-plays, and public commitments to utilize new skills.

Both female and male trainers facilitated the sessions with a trainer:student ratio of approximately 1:15. Trainers were chosen through an intensive interview and vetting process to ensure that they were respected members of their communities and had a background in health improvement. All trainers received extensive instruction by expert facilitators, and participated in mock interviews and field training exercises conducted outside of the study area. Trainers were required to pass written and oral examinations, as well as a physical skills demonstration before teaching the curriculum. The training and field exercises combined took approximately 1 year to complete before trainers were allowed to teach classes as the main trainer.

### Standard of care

The SOC group received a one-time 1.5–2-h life skills class that is supported by the Kenyan Ministry of Education and includes a wide range of topics, including sexual assault, sanitation, food safety, and personal rights. All school-aged children who attend an accredited school typically receive this curriculum. Thus, participants in the intervention arm are likely to also receive the SOC at some point in their educational careers. These sessions were taught by trained NMNW facilitators on school property for consistency.

After the completion of the study and post-final data collection, NMNW trained facilitators provided a sample of schools in the SOC arm of the study with the intervention.

### Timeline

Because Ujamaa had a core cadre of very experienced trainers who had undergone extensive preparation, as described above, we did not want to threaten the quality of the intervention by bringing in many new trainers. Therefore, we divided the schools into three cohorts, so each group could be trained by the existing experienced trainers. The cohorts were rolled-out between January–September of 2016, with 12 and 24 month follow-up between January–September of 2017 and 2018, respectively.

### Quantitative data collection and analysis

#### Survey development

There are very few validated scales available for this group (10–14 year old girls) regarding sexual abuse, and variables on the pathways to sexual abuse. Therefore, we drew from a variety of sources in creating our surveys. In order to measure the primary outcome, change in incidence of self-reported sexual assault among girls from baseline, we created an index based on several variables. Key surveys that informed these questions included the Kenya VACS [34] and surveys from the Stepping Stones project in South Africa [16, 35]. These items include both experiences of IPV (for example, “In the past 12 months, how many times has your current or a previous boyfriend physically forced you to have sex when you did not want to?” and “In the past 12 months, how many times has your current or a previous boyfriend used threats or intimidation to get you to have sex when you did not want to?”) as well as sexual violence by non-partners (“In the past 12 months, how many times has a man who is NOT your boyfriend forced or persuaded you to have sex against your will?” and “In the past 12 months how many times was there an occasion when you agreed to have sex with one man or boy and one or more others who you had not agreed to have sex with forced you to have sex with them as well?”).

Validated, widely used scales were more readily available for some of the secondary outcomes. Specifically, we used the “Self-Efficacy Questionnaire for Children” [36], for self-efficacy, and the “Rosenburg Self-Esteem Scale” [37], for self-esteem. For experiences of social and emotional violence, we relied on the VACS and Stepping Stones surveys. For gender norms and relations, some questions were removed from existing surveys and modified for this population during piloting, and others were created based on the field team’s knowledge of this population, then modified during piloting. We also collected data on acceptability of the program and how often adolescents recall using specific skills from the program.

#### Baseline analysis

The baseline data collected were analyzed to provide insights into the prevalence and characteristics of violence in these settlements. Summaries of: (i) demographic information of participants, (ii) rates of intimate partnerships, (iii) baseline rates of violence (non-GBV), (iv) baseline rates of GBV (non-rape), (v) baseline rate of rape, (vi) distribution of count of rapes (i.e., some participants will be raped many times and some not at all, we will summarize this distribution), (vii) distributions of self-efficacy and self-esteem, and (viii) distribution of perpetrators. Further, we used a principal stratification approach to estimate the relationship between hypothesized intermediate effects – self-efficacy, alcohol use, gender norms, and self-esteem – and rape [38]. The analysis of hypothesized intermediate effects informed the discussion of causal pathways from the intervention to the outcome (related to “structural equation modeling” approaches, or “mediation analysis”).

#### Outcome analysis

We used an intention to treat (ITT) estimand to analyze the primary outcome of change in incidence of self-reported sexual assault among adolescent girls from baseline. An instrumental variable (IV) analysis was also proposed as a secondary analysis to estimate the effectiveness of the intervention [39], but was not tenable because trainee-attendance records were not well-maintained.

We estimated the effect of the intervention on the rate of sexual assault on the participant level using generalized linear mixed models (GLMM), with each participant’s survey being a unique observation in the model. Note that the analyses were stratified by sex – models were run separately for girls and for boys. The outcome of interest was binary and thus will be modeled using a logistic link function. Missing covariate values were addressed using multiple imputation models.

The estimand of interest was a repeated measures effect, the change of incidence of sexual assault between the prior twelve-month period at baseline as compared to the twelve-month period between the first follow-up period and the final follow-up period on the participant level. In our GLMM, repeated measure effects were added to the model for individual girl, school, and matched set. Fixed effects were added for period (i.e., baseline, first follow-up and end of study), intervention level, and an interaction for period and intervention level. The coefficient for the interaction term between period and intervention level was our estimate of interest. The GLMM was chosen in order to facilitate comparisons with other interventions in the What Works to Prevention Violence Against Women and Girls consortium. A GEE model of the main outcome was performed as a sensitivity analysis.

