## Methods/design

### Study design

This was a two-arm, parallel, cluster-randomized trial with clusters defined as schools within the settlements. Data collection began in January 2016 and continued through December 2018.

The study was conducted in six informal settlements in Nairobi: Kibera, Mukuru, Huruma, Dandora, Kariobangi, and Korogocho. For the purposes of the study, given the small number of schools from Kariobangi, Kariobangi schools were considered part of the Dandora settlement. Local partners included three non-governmental organizations, No Means No Worldwide (NMNW), Ujamaa Africa, and the African Institute for Health and Development (AIHD). NMNW created the intervention, Ujamaa implemented the intervention, and AIHD was the Nairobi-based research partner for the evaluation component of the study. Stanford University was the independent, external evaluator of the intervention.

The primary outcome was the change in incidence of self-reported sexual assault among adolescent girls from baseline, comparing the IMpower and SOS interventions to a SOC intervention. Secondary outcomes included determining the impact of the interventions on self-efficacy, self-esteem, gender attitudes and beliefs, and experiences of physical and emotional violence. We also measured episodes of perpetrating violence and bystander behaviors among adolescent boys. In follow-up surveys, we collected data on acceptability of the program and how often adolescents recall using specific skills from the program. All of these data were collected using quantitative surveys. We also collected process data at follow-up on what components of the intervention the adolescents found useful and what the adolescents suggest changing about the intervention in the future. Stakeholder meeting of teachers, head teachers, and officials from the Kenyan Ministry of Education were held before each round of data collection to answer questions and gain buy-in.

We also collected qualitative data through in-depth interviews with both girls and boys. These focused on the experiences and understanding of violence in the communities, as well as characteristics of implementation to gain a deeper understanding of successes and failures of the intervention.

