### Sample size

We powered the study to distinguish the intervention from the SOC group based on the sexual assault prevention outcome. Based on our 2013–14 pilot study, we assumed that baseline annual incidence in similar informal settlements, in this age group, is 7.3% [6]. From this prior study, we also estimated the interclass correlation to be approximately 0.001.

We calculated sample size to achieve 80% power of detecting approximately a 40% decrease in the odds of sexual assault as reported by the participants when comparing the intervention group to SOC group (technically, calculated as a risk difference from 0.07 to 0.044). We took into account a school-level dropout of 25% and a participant-level dropout of 25% over the course of the study. Calculations to determine the sample size were run using the *CRTSize* package in R, function *n4props()* [31]. Given the above assumptions, we estimated that we needed a minimum of 45 schools for each arm of the trial, with at least 40 girls in each school.

We also recruited male participants into the study to complete surveys in order to better understand their experiences of violence in this setting. As this is an exploratory aim, this study is not powered on boys’ outcomes. The specific number of boys studied in each school was maximized given restrictions due to funding; we randomly sampled between 5 and 15 boys per school and included all of the sampled schools that had boys enrolled in class 6.

For the qualitative data, we purposively sampled 20 girls and ten boys from one participating school in the Dandora neighborhood to participate in in-depth interviews. This sampling approach was taken in order to allow for deep understanding of one of the study communities.

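### The primary GLMM, as listed, names no school-by-period effect, so on its natural reading the standard error of the period-by-intervention interaction omits between-school variation in change

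*Protocol article*

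**What the plan says.** The article describes a "two-arm, parallel, cluster-randomized trial with clusters defined as schools within the settlements" (Study design). Under Outcome analysis, each survey of each girl is one observation in a logistic mixed model, and "repeated measure effects were added to the model for individual girl, school, and matched set". The fixed part is also listed: "Fixed effects were added for period (i.e., baseline, first follow-up and end of study), intervention level, and an interaction for period and intervention level". The tested quantity is then named: "The coefficient for the interaction term between period and intervention level was our estimate of interest". No school-by-period effect, school slope or school-level robust variance appears. The words random intercept do not appear either. The only other model of the main outcome is given in one sentence: "A GEE model of the main outcome was performed as a sensitivity analysis".

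Under Sample size, the ICC comes from the 2013–14 pilot: "we also estimated the interclass correlation to be approximately 0.001". The Background (Knowledge gaps) says that the earlier randomized trial was an open cohort that did not follow individual girls over time, and that follow-up in the earlier studies reached 10 months at most.

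**The concern.** The primary estimate is a difference between arms in change over time. An effect that takes the same value for a girl, school or matched set at every period shifts all of its observations equally, so it contributes nothing to that contrast. Because schools were randomized, the relevant school-level noise is how differently schools change between baseline and the end of study for reasons unrelated to the intervention. With time-constant effects only, that variation has no term of its own. It falls into the girl-level residual, where it is averaged as if it were independent between girls in the same school.

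The article itself gives reasons to expect shared change. Training is delivered to groups (Intervention), boys in the same school are trained as bystanders (Intervention; Discussion), and engaging teachers and headmasters may itself have a preventive effect (Limitations). At stake is the validity of the confidence interval and p-value for the one coefficient on which the trial's main conclusion depends.

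**Working it through.** **Inputs from the article.** At least 40 girls per school, 25% participant dropout, 25% school dropout, at least 45 schools per arm, ICC about 0.001, 80% power, and an effect size "technically, calculated as a risk difference from 0.07 to 0.044" (all Sample size). After participant dropout, m = 40 × 0.75 = 30 girls per school.

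**Assumptions, not in the article.** Two-sided alpha 0.05; ICCs of 0.01 and 0.02 as alternatives to 0.001; the share of school variance that is constant over time (CAC), base case 0.5; the correlation between two reports by the same girl (r), base case 0.3.

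**1. The plan's own figure.** Girls per arm before clustering: (1.960 + 0.842)² × (0.07 × 0.93 + 0.044 × 0.956) / 0.026² ≈ 1,244.
- With m = 40: 1,244 × (1 + 39 × 0.001) / 40 = 32.3 schools; divided by 0.75 this is 43.1, so 44 per arm, one short of the stated 45.
- With m = 30 and no school dropout: 1,244 × 1.029 / 30 = 42.7, so 43.
- With m = 30 and school dropout as well: 56.9, so 57.

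The stated 45 is thus nearly reproduced under some readings of the dropout allowance. In all of them the ICC enters only as clustering of levels at one time point. The present point does not depend on which reading applies.

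**2. Variance of the change contrast.** Let ρ be the school ICC within a period. Per school and up to a common factor, the girl-level part of the variance of a mean change is (1 − ρ)(1 − r)/m, and the school-by-period part is ρ(1 − CAC). A model with time-constant effects carries only the first part. Hence

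true variance / model variance = 1 + mρ(1 − CAC) / [(1 − ρ)(1 − r)],

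type I error = 2[1 − Φ(1.96 / √ratio)].

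Base case, m = 30, CAC = 0.5, r = 0.3:

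| ICC | Ratio | Type I error | Model variance too small by (1 − 1/ratio) |
|---|---|---|---|
| 0.001 (article) | 1 + 0.015/0.6993 = 1.02 | 5.2% | 2% |
| 0.01 (assumed) | 1 + 0.150/0.693 = 1.22 | 7.6% | 18% |
| 0.02 (assumed) | 1 + 0.300/0.686 = 1.44 | 10.2% | 30% |

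The excess of the true variance over the model's is 22% and 44%; the model's shortfall is 18% and 30%.

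**3. Sensitivity.** If the school-by-period variance is allowed to inflate the model's residual, the denominator becomes [(1 − ρ)(1 − r) + ρ(1 − CAC)]/m. The base-case ratios are then (0.0231 + 0.005)/0.02327 = 1.21 at ICC 0.01 and (0.02287 + 0.01)/0.0232 = 1.42 at ICC 0.02, little different. With this second formula, over m of 30 or 40 and the combinations of CAC (0 to 0.8) and r (0 or 0.3) that were run:
- ICC 0.001: at most 5.6%, reached with m = 40, CAC = 0 and r = 0.3.
- ICC 0.01: 5.7% to 11.6%.
- ICC 0.02: 6.4% to 17.7%.

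**4. Simulation check.** Binary outcomes under the null at two periods, 4,000 runs per setting, incidence about 6% to 7%. The interaction was tested by within-girl conditional logistic regression, from which all girl, school and set intercepts drop out exactly. This stands in for the intercept-only GLMM, which was not itself fitted. With 34 schools per arm and 30 girls per school:
- ICC about 0.01, school effect constant over time: 5.3%.
- ICC about 0.01, half period-specific: 6.8%; all period-specific: 8.5%.
- ICC about 0.02, half period-specific: 8.4%; all period-specific: 12.1%.

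At ICC about 0.001 with some or all of the school variance period-specific, results were 4.4% to 5.1%, including one setting with 45 schools of 40 girls. A t-test on school mean changes, which carries school-by-period variance, stayed between 4.2% and 5.2% in every setting.

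**The case against.** The strongest objection is that the article never says the effects are random intercepts. A repeated-measures effect for school could mean one that varies by period, and a condensed article may leave the covariance structure to a fuller document. This stands as a limit on the claim: the time-constant reading is an inference. It is the natural one because the model's terms are listed and none is a school-by-period term.

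Second, a reader might infer that the primary analysis ignores clustering, or that variation in change cancels. The documents do not support either. School and matched set are both in the model. What cancels is the constant school level; variation in change remains in the data and is left unmodelled.

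Third, the only documented ICC gives no material inflation, and the larger figures need ICCs 10 and 20 times as high. This also stands. However, that ICC describes clustering of levels, from a trial that did not follow individual girls and within earlier work that reached 10 months at most. It does not measure school-to-school variation in change over 24 months.

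Fourth, a school-by-period variance would be weakly identified. With 30 girls and incidence of 4.4% to 7%, each school-period has 30 × 0.044 = 1.3 to 30 × 0.07 = 2.1 events, so the variance may be estimated at zero, which returns the same model. This is a fair argument against relying on that term alone. It does not touch school-level robust errors or permutation.

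Finally, the unstated cluster level of the GEE is missing detail, not an error, and is not counted here.

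**Conclusion.** The point holds conditionally. If the listed effects are constant over time, the standard error of the primary interaction omits between-school variation in change, and the test is anti-conservative whenever such variation exists. At the article's ICC the consequence is negligible. At assumed ICCs of 0.01 and 0.02, with half the school variance period-specific, a within-girl correlation of 0.3 and 30 girls per school, the nominal 5% test runs at about 7.6% and 10.2%. The documents supply neither those ICCs nor the other two parameters, so nothing here shows that this trial's error rate is in fact inflated. The case for a change is that the primary test need not depend on a small ICC from a shorter study without individual follow-up when protection is cheap. This is a worthwhile improvement rather than a fatal flaw.

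**What to change.** Base inference for the period-by-intervention interaction on a method that carries between-school variation in change. Any one of these would serve:
- a random school-by-period effect added to the GLMM, with one of the next two as the stated fallback if its variance is estimated at zero or the model does not converge;
- standard errors for the interaction that are cluster-robust at school level;
- a permutation test that swaps arms within matched sets, restricted to allocations that the balance rule under Randomization would have accepted.

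Cluster the GEE sensitivity analysis on school, so that it covers the same source of variation. If the fitted model already lets the school effect vary by period, one sentence saying so settles the point.

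The GLMM can remain the source of the point estimate, which keeps the comparability with the consortium's other trials that the article gives as its reason for choosing it. The cost is a slightly wider interval and some extra analysis work. If the true ICC is near 0.001 the interval should barely change, since the base-case variance ratio is 1.02.

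### The estimand is a change in 12-month incidence, but the named estimate is a conditional log odds ratio, with no stated step back to incidence

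*Protocol article*

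**What the plan says.** In the protocol article, Outcome analysis states the target as follows: "The estimand of interest was a repeated measures effect, the change of incidence of sexual assault between the prior twelve-month period at baseline", set against the twelve months between the first and the final follow-up, at participant level. The abstract, Study design and Survey development also name the primary outcome as a change in incidence.

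The model is a GLMM: "The outcome of interest was binary and thus will be modeled using a logistic link function", and "repeated measure effects were added to the model for individual girl, school, and matched set". Fixed effects are period (three levels), intervention and their interaction. The estimate is then named: "The coefficient for the interaction term between period and intervention level was our estimate of interest". The reason given for the model is comparability: "The GLMM was chosen in order to facilitate comparisons with other interventions" in the same consortium. A population-averaged model appears only in a supporting role: "A GEE model of the main outcome was performed as a sensitivity analysis".

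Sample size gives the target effect as roughly 40% lower odds, with the parenthesis "technically, calculated as a risk difference from 0.07 to 0.044". Under Knowledge gaps, the background reports the pilot result as a fall of 3.7 percentage points from 7.3%.

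**The concern.** A change in incidence is a difference between proportions of girls. The interaction coefficient of a logistic mixed model differs from it in two ways. It is a ratio of odds ratios on the log scale, and it is conditional on the girl effect, so it compares odds at a fixed level of a girl's latent risk. Odds ratios are non-collapsible: when girls differ in underlying risk, the conditional odds ratio and the population odds ratio are different numbers even if the model is exactly right.

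If the coefficient is the only effect size reported, the trial does not report the quantity it defines. The size of the effect cannot then be set directly against the pilot's percentage-point fall or the two rates in Sample size. A gap between the GLMM and the GEE could also be taken for lack of robustness when part of it is a change of scale.

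**Working it through.** **Inputs from the article.** Target rates 0.07 and 0.044, and school intraclass correlation about 0.001 (Sample size). Logit link and effects for girl, school and matched set (Outcome analysis). The girl-level SD on the logit scale is not given, so a range is assumed.

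**Step 1: the plan's own effect.**
- Risk difference: 0.07 − 0.044 = 0.026.
- Risk ratio: 0.044/0.07 = 0.629.
- Marginal odds ratio: (0.044/0.956)/(0.07/0.93) = 0.0460/0.0753 = 0.611, or 38.9% lower odds.

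The stated reduction of about 40% in the odds therefore agrees with the stated rates. Sample size contains no error on this point.

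**Step 2: the conditional odds ratio for the same two rates.** Assume both arms start at 0.07, SOC stays there and intervention falls to 0.044. For a normal girl effect with SD s, the population risk at conditional logit η is p = E[1/(1 + exp(−(η + sZ)))], with Z standard normal. Solve for η at p = 0.07 and at p = 0.044 by Gauss-Hermite quadrature. The conditional odds ratio is exp(η₂ − η₁). The implied fall is what results if that odds ratio is applied to 7.0% as though it were marginal; the true fall is 2.6 points.

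| Girl SD (assumed) | η₁ | η₂ | Conditional OR | Lower odds | Implied fall (points) | Ratio to 2.6 |
|---|---|---|---|---|---|---|
| 0 | −2.587 | −3.079 | 0.611 | 38.9% | 2.6 | 1.00 |
| 0.5 | −2.692 | −3.191 | 0.607 | 39.3% | 2.6 | 1.01 |
| 1 | −2.989 | −3.514 | 0.592 | 40.8% | 2.7 | 1.05 |
| 1.5 | −3.425 | −3.999 | 0.563 | 43.7% | 2.9 | 1.13 |
| 2 | −3.951 | −4.595 | 0.525 | 47.5% | 3.2 | 1.23 |
| 2.5 | −4.536 | −5.262 | 0.484 | 51.6% | 3.5 | 1.34 |

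To judge which SD is plausible: SDs of 1, 1.5, 2 and 2.5 mean that 14%, 22%, 31% and 39% of girls assaulted in one year would be assaulted in another, against 7% overall. The article gives no such figure.

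**Step 3: the school effect.** An intraclass correlation of 0.001 at p = 0.07 corresponds to a logit variance of about 0.001/(0.07 × 0.93) = 0.015, an SD of 0.124. The conditional odds ratio is still 0.611, so any gap comes from the girl effect.

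**Step 4: direction when baselines and trend differ.** Assumed rates: SOC 0.07 to 0.03, intervention 0.10 to 0.05.
- Incidence scale: (0.05 − 0.10) − (0.03 − 0.07) = −0.01, which favours intervention.
- Odds scale, no random effects: intervention (0.05/0.95)/(0.10/0.90) = 0.474; SOC (0.03/0.97)/(0.07/0.93) = 0.411; ratio 0.474/0.411 = 1.15, which favours SOC.

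The two contrasts can thus differ in sign. This example is deliberately unbalanced at baseline and shows only what is possible.

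**The case against.** A conditional odds ratio is a legitimate estimand, not a biased marginal one. The article nowhere applies it to 7% or reads it as a change in percentage points. The sample-size target is itself worded in odds. The estimand is called a repeated-measures effect at participant level, which could be taken to mean a within-girl contrast. A GEE is planned, the choice of GLMM is explained, and absolute effects are often left to an analysis plan or results paper.

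Much of this stands. The test is sound, the target is coherent, the GLMM has a stated purpose, and no figure in the article is wrong.

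Two things do not follow. Participant level says at which level the data are modelled; it does not make a conditional log odds ratio a change in incidence. And this is more than an omitted detail, because the article names both the estimand and the estimate, and they are different quantities. The GEE does not close the gap either: it is not primary, and with a logit link it would still give an odds ratio.

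A reader might infer more: that the plan overstates the protective effect, that the trial was sized on a risk difference alone, or that clustering by school drives the gap. The documents support none of these. Overstatement requires someone to read the coefficient as the population change, comparable baselines, and a girl-level SD well above 1 that the article does not give. Sample size also states odds, and they agree with its rates. At the stated intraclass correlation the school effect contributes nothing visible.

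**Conclusion.** The point holds as a mismatch of scale between estimand and reported estimate. It is not an error in the test or in the sample-size target.

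With comparable baselines and differences in risk between girls, the coefficient lies further from zero than the marginal log odds ratio. For the planned effect the gap is negligible up to SD 1 (41% against 39% lower odds) and becomes material around SD 2 (47.5%) and 2.5 (51.6%). These figures rest on a normal girl effect, equal baselines, no change in SOC, and an SD that is assumed throughout. Baseline analysis expects some girls to be assaulted many times and others not at all. That makes heterogeneity plausible, but it concerns counts within a period and does not fix the SD. Under unequal baselines or a secular trend, the difference can go either way.

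The change is worth making because the trial is presented as a replication of the pilot, whose result is in percentage points.

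**What to change.** Keep the GLMM, the interaction test and the conditional odds ratio, which serves the consortium comparison. Add to Outcome analysis that the effect size for the stated estimand is the between-arm difference in change in 12-month incidence, end of study minus baseline. Obtain it from the fitted model by averaging predicted probabilities over the random-effect distribution, with a delta-method interval or a school-level bootstrap that respects the matched sets. Use this figure for comparison with the pilot. Compare the GEE with the GLMM only after both are on this scale.

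The cost is one post-estimation step and a sentence or two of text, with no new data and no change to the p-value. The downside is that the reported effect may look slightly smaller than the conditional odds ratio suggests.
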